**Results:**

We hypothesize that (1) at least 50% (n=5) of eligible clinics and 50% (n=40) of eligible patients who are invited will participate, and at least 70% (n=56) of patients will complete the program, and (2) patients who receive the intervention will have improved self-care behaviors and clinical test results with at least 75% (n=60) of the patients maintaining improved outcomes at follow-up visits compared with baseline, and participants will verbalize that the intervention is feasible and acceptable. As of August 2023, we enrolled 10 clinics and 60 patients. Baseline data results will be available by the end of 2023 and outcome data will be published in 2025.

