#### Patient Recruitment and Consent Process

This study will recruit 80 patients from 10 clinics, approximately 8 patients from each clinic. We expect to have approximately 5 to 6 patients complete this study from each clinic giving a 70% (n=56) study completion rate. The power calculation was conducted by using the linear mixed effect modeling of the R (R Foundation for Statistical Computing) package “*swdpwr*,” which gives power of 0.95 for the alternative hypothesis treatment effect change of 0.005 (2-sided type I error 0.05). The recruitment strategy includes a letter and flyer to be sent by the clinics with the research team’s contact information. Study information will be provided to those who reach out to a research team member with their interest and an opt-out contact will be applied after 3 days of receiving the letter. A member of the research team will arrange a time to meet with eligible patients to discuss the option to participate in this study, complete the informed consent procedure, complete this study’s screener, and enroll them in this study if the individual is both eligible and interested. All patients will have the option of completing the consent and confidentiality forms in English or Vietnamese language. Upon full study enrollment, a member of the research team will collect baseline data.

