The secondary outcomes are self-reported changes in behaviors and clinical test results, which will be compared to determine intervention maintenance and effectiveness. Repeated outcome measures will be assessed at 5 points in time. The translated and validated SDSCA revised scale [32] will be used to measure behavioral changes and assess 5 topics: diet, physical activity and exercise, blood glucose testing, foot care, and smoking. The average interitem correlations within scales were high (mean *r*=0.47) with the exception of specific diet; test-retest correlations were moderate (mean *r*=0.40). Correlations with other measures of diet and exercise generally supported the validity of the SDSCA subscales (mean *r*=0.23). Triglyceride, low-density lipoprotein, high-density lipoprotein, hemoglobin A_1c_, BMI, weight, and blood pressure will be used to measure clinical changes, which will be obtained from the participants’ medical records. Participants will be monitored for an additional 9 months via chart reviews and self-report using the SDSCA scale to determine whether any improvements observed at completion of the intervention will still be evident.

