#### Data Analysis

To evaluate the first hypothesis, descriptive statistics will be used to analyze the acceptability and feasibility of the intervention, which include the proportion of individuals who met the criteria, proportion of eligible participants who agreed to participate, the proportion of mHealth responses completed, and attrition rate at follow-up periods. A linear regression model will be used to examine the association of response rate and attrition rate with other predictors. To evaluate the second hypothesis, continuous variables will be calculated using descriptive statistics including quantiles, mean, and SD. To examine the association of continuous outcome variables and other predictors, a linear mixed effect model will be used to examine time effects, clustering effects, and the interaction of the two. Transformation of outcome variables will be conducted to normalize the nonnormal distributions. To examine the association of categorical outcome variables and other predictors, a generalized linear mixed effect model will be used to examine time effects, clustering effects, and the interaction of the two. In order to handle missing values, sequential multiple imputation will be performed before the analysis. SAS (version 9.4; SAS Institute) will be used for statistical analysis.

To analyze qualitative data from the focus groups and interviews, field notes will be transcribed for coding and analysis. Focus groups and interviews conducted in Vietnamese will be translated into English by the research assistant and verified by the PI before coding and analyzing thematically. Prior to analyzing the transcripts, the researchers will read the transcripts at least twice and compare them with the field notes to ensure accuracy and completeness. Selected transcripts will be reviewed by an experienced qualitative researcher to compare the consistency in developing a coding schema. The NVivo (Lumivero) software will be used to manage and analyze qualitative data.

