## Discussion

This study is driven by two hypotheses: (1) at least 50% (n=5) of eligible clinics and 50% (n=40) of eligible patients who are invited will participate, and at least 70% (n=56) of patients will complete the program, and (2) patients who receive the intervention will have improved self-care behaviors and improved clinical test results with at least 75% (n=60) of the patients maintaining improved outcomes at follow-up visits compared with baseline, and participants will verbalize that the intervention is feasible and acceptable. This protocol was designed with an interprofessional research group that has many strengths. An overall strength is the stepped wedge design, which allows participating clinics to be randomized with an opportunity for all consented patients to participate in the intervention. The staggering of clinic implementation allows the research team to train clinic staff and monitor potential implementation issues. The mixed method and longitudinal design provide insights into long-term outcomes over time.

Another strength of this protocol is this is the first Vietnamese DSMES intervention to be implemented in collaboration with primary care clinics that leverages mHealth technology to address the barriers of language and cultural differences. Vietnamese-speaking individuals have few opportunities to participate in health-related randomized clinical trials. This protocol allows that opportunity because it is offered in the Vietnamese language to promote self-determination and independence, and improve self-management strategies.

Further, 1 limitation of the stepped wedge design is that patients of clinics that were randomized for implementation later will have to wait months before receiving the intervention. This waiting period may reduce engagement with the researchers and may increase attrition rates. Another limitation is the repeated measurements of questionnaires and clinical tests may lead to a higher respondent burden on patients and clinic staff.

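### The maintenance target of 75% (n=60) is counted on all 80 enrolled patients and does not fit the plan's own expectation that 56 of them complete the study

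*Protocol article*

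**What the plan says.** The section on patient recruitment and consent sets the sample: "This study will recruit 80 patients from 10 clinics, approximately 8 patients from each clinic". It goes on: "We expect to have approximately 5 to 6 patients complete this study from each clinic giving a 70% (n=56) study completion rate".

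The Discussion states two hypotheses. The first includes a completion criterion: "at least 70% (n=56) of patients will complete the program". The second includes a maintenance criterion: "with at least 75% (n=60) of the patients maintaining improved outcomes at follow-up visits compared with baseline". The Results paragraph of the Abstract gives the maintenance criterion with the same percentage and count: "at least 75% (n=60) of the patients maintaining improved outcomes at follow-up visits compared with baseline".

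Outcome Measures names maintenance as one of the five RE-AIM domains that make up the primary outcomes. On how it is followed, it says: "Participants will be monitored for an additional 9 months via chart reviews and self-report using the SDSCA scale". The patient-level maintenance row of Table 1 lists clinical assessments and laboratory results as the data source. On missing data, the Data Analysis section says: "In order to handle missing values, sequential multiple imputation will be performed before the analysis".

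The article does not say in words which patients form the denominator of the 75%, or whether a patient who does not complete can count as having maintained an improvement.

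**The concern.** The counts in the hypotheses describe successive stages: patients enrol, some complete, and some of those hold an improvement at later visits. Such counts should stay level or fall from stage to stage. Here the count rises from 56 completing to 60 maintaining.

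The 75% is a printed success criterion for one of the two hypotheses that the study says drive it, and it belongs to a primary RE-AIM domain. Without a stated denominator, one result can pass or fail depending on who is counted. Suppose 45 patients maintain an improvement among 56 completers. That is 45/56 = 80% of completers, which meets 75%, but 45/80 = 56% of those enrolled, which does not. If the denominator is settled only after the data are seen, the conclusion on this hypothesis is open to choice.

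**Working it through.** **Inputs**

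- Planned enrolment: 10 clinics × about 8 patients = 80 (Patient Recruitment and Consent Process).
- Expected study completion: 70%, n=56 (same section).
- Maintenance target: 75%, n=60 (Discussion; Abstract, Results).

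**Reproducing the printed counts**

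- 0.70 × 80 = 56, as printed.
- 0.75 × 80 = 60, as printed.

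Both counts are therefore percentages of all 80 enrolled. The 60 is not a percentage of those expected to complete.

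**Setting the two side by side**

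- Excess of target over expected completers: 60 − 56 = 4 patients; 60/56 = 107%.
- Highest all-enrolled proportion if all 56 completers maintain and no one else counts: 56/80 = 70%, below 75%.
- Lowest completion at which 60 can be reached: 60/80 = 75%.

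**What share of completers must maintain to reach 60 (60 ÷ completers)**

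| Completers | Completion, of 80 | Share of completers needed |
|---|---|---|
| 50 | 62.5% | 120% (not reachable) |
| 56 | 70% | 107% (not reachable) |
| 60 | 75% | 100% |
| 64 | 80% | 93.75% |
| 72 | 90% | 83.3% |
| 80 | 100% | 75% |

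The rows for 50 and 60 are the two ends of the plan's 5 to 6 completers per clinic (10 × 5 and 10 × 6). At the upper end, every completer would still have to maintain. The 75% and n=60 describe the same requirement among completers only if nobody is lost.

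**The other denominator**

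- 75% of the expected 56 completers: 0.75 × 56 = 42.
- The same 42 as a share of all enrolled: 42/80 = 52.5%.

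The two readings of one sentence thus differ by 60 − 42 = 18 patients.

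**The case against.** A reader might infer that hypothesis 2 cannot be met, or is certain to fail. The article does not support that, for three reasons.

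- The completion figure in hypothesis 1 is a minimum, and the recruitment section's figure per clinic is approximate, spanning 50 to 60 patients. Retention of 75% or more is possible, so the two hypotheses are not logically incompatible. This stands. It leaves untouched that 56 is the number the plan expects.
- Patients who stop the 12-week program are not necessarily lost to observation. Maintenance is followed partly by chart review, Table 1 points to clinical and laboratory data for it, and missing values are to be imputed. A non-completer could therefore have a chart value or an imputed one. This also stands, as a reason to state the conclusion conditionally. It does not resolve the conflict: nothing in the article says that such patients count towards the 60, the 56 is also described as completion of the study and not only of the program, and maintained self-care behaviour on the SDSCA needs self-report.
- The bracketed counts may be mechanical conversions of each percentage into a share of 80. The same sentence gives 40 as half of the eligible patients invited, although 80 is the number to be recruited. On this view the criterion is the percentage, it is attainable among patients with follow-up, and only the bracket is wrong. That may be what was meant. It is still a wrong number, printed twice.

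The weight of the point should not be overstated either. No stopping rule, significance test or sample size rests on the 75%, and the power statement does not use it.

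**Conclusion.** The point holds in conditional form. The maintenance target of 75% (n=60) is taken on all 80 enrolled and is inconsistent with the plan's expectation that 56 of 80 complete. At that retention, and if maintenance must be observed in completers, the ceiling is 70%, which is 5 percentage points or 4 patients short. The target becomes reachable at 75% retention with no failures among those retained, and needs 93.75% of completers to maintain at 80% retention.

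The conclusion rests on two assumptions: that retention is as the plan expects, and that non-completers do not count as maintained. The article states the first and is silent on the second.

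This is a wrong or undefined number in a stated success criterion, not detail that an article would leave to a fuller document. It does not affect the design, the sample size or the data collected.

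**What to change.** Before outcome data are analysed, state the denominator of the 75% and how non-completers count, including whether chart values or imputed values can make a patient a maintainer. Then make the count agree in the Abstract and the Discussion. The choice between the two readings is the sponsor's:

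- **Patients with follow-up data.** Replace n=60 with 42 of the expected 56. Report beside it the proportion of all enrolled, with non-completers counted as not maintained.
- **All 80 enrolled.** Either keep n=60 and say that it requires retention above the expected 70% (at least 75%, and more unless every retained patient maintains), or lower the percentage to one compatible with 56 completers. That means no more than 70%, and 70% itself would allow no failures among completers.

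The cost is a text correction in two places. The downside of the first option is that it is the more favourable denominator and lowers the count from 60 to 42 while the trial is under way. For that reason the change should be dated and explained, and the all-enrolled figure should always appear with it.

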## Abbreviations

DSMES: diabetes self-management education and support
mHealth: mobile health
PI: Principle investigator
RE-AIM: Reach, Effectiveness, Adoption, Implementation, Maintenance
SDSCA: Summary of Diabetes Self-Care Activities
SMart-D: Self-Management mobile health Intervention for US Vietnamese with Diabetes
SPIRIT: Standard Protocol Items: Recommendations for Interventional Trials
T2D: type 2 diabetes
